## Abstract

**Background:**

Management of high-risk newborns should involve the use of standardized protocols and training, continuous and specialized brain monitoring with electroencephalography (EEG), amplitude integrated EEG, Near Infrared Spectroscopy, and neuroimaging. Brazil is a large country with disparities in health care assessment and some neonatal intensive care units (NICUs) are not well structured with trained personnel able to provide adequate neurocritical care. To reduce this existing gap, an advanced telemedicine model of neurocritical care called *Protecting Brains and Saving Futures (PBSF) Guidelines* was developed and implemented in a group of Brazilian NICUs.

**Methods:**

A prospective, multicenter, and observational study will be conducted in all 20 Brazilian NICUs using the *PBSF Guidelines* as standard-of-care. All infants treated accordingly to the guidelines during Dec 2021 to Nov 2024 will be eligible. Ethical approval was obtained from participating centers. The primary objective is to describe adherence to the *PBSF Guidelines* and clinical outcomes, by center and over a 3-year period. Adherence will be measured by quantification of neuromonitoring, neuroimaging exams, sub-specialties consultation, and clinical case discussions and videoconference meetings. Clinical outcomes of interest are detection of seizures during hospitalization, use of anticonvulsants, inotropes, and fluid resuscitation, death before hospital discharge, length of hospital stay, and referral of patients to specialized follow-up.

**Discussion:**

The study will provide evaluation of *PBSF Guidelines* adherence and its impact on clinical outcomes. Thus, data from this large prospective, multicenter, and observational study will help determine whether neonatal neurocritical care via telemedicine can be effective. Ultimately, it may offer the necessary framework for larger scale implementation and development of research projects using remote neuromonitoring.

**Trial registration:**

NCT03786497, *Registered 26 December 2018*, https://www.clinicaltrials.gov/ct2/show/NCT03786497?term=protecting+brains+and+saving+futures&draw=2&rank=1.

## Introduction

Neonates requiring intensive care are exposed to a variety of interventions and treatments that improves survival but can affect their neurological system. Epidemiological studies indicate that every year 1.15 million infants suffer a hypoxic-ischemic event at birth and 13 million are born prematurely [1–5]. Of these, a substantial number will develop moderate or severe neurological impairment. Furthermore, other disorders such as congenital heart disease, cerebral malformations, congenital and nosocomial infections, intraventricular hemorrhages, inborn errors of metabolism, seizures, and severe hemodynamic and ventilatory instability can compromise brain integrity and function [6–8]. Modern neonatal intensive care units (NICU) can provide strategies to prevent neurological impairment using standardized clinical protocols and training, neuromonitoring, and neuroimaging; the so called neonatal neurocritical care units or neuroNICUs.

Amplitude Integrated Electroencephalography (aEEG) is a non-invasive methodology for continuous monitoring of brain function at the bedside, specifically for determination of electrical background activity and sleep-wake cycle (SWC) patterns, and detection of seizures [9, 10]. Indeed, the use of a two-channel aEEG with raw EEG readings (aEEG/EEG) has showed improved accuracy for the detection of seizures on real-time [11, 12], an important effect as seizure burden is an independent risk factor for neurodevelopmental delay [13–16] and treatment of subclinical seizures is associated with improved neurodevelopmental outcomes [17]. Moreover, in infants with hypoxic ischemic encephalopathy (HIE), aEEG findings have good predictive value for neurological short- and long-term outcomes [18–21].

Another available methodology for brain monitoring at the bedside is the Near Infrared Spectroscopy (NIRS), a non-invasive tool that provides continuous measurements of cerebral tissue oxygenation and perfusion (rSO2). NIRS evaluates the balance between tissue oxygen delivery and consumption allowing the early identification of perfusion abnormalities and hemodynamic changes [22, 23]. Therefore, NIRS monitoring is important in several clinical scenarios including HIE, prematurity, shock, anemia, congenital heart disease and other cases that lead to hemodynamic and ventilatory instability [24–26].

According to the World Health Organization (WHO), telemedicine is defined as the delivery of health care services, where distance is a critical factor, by all health care professionals using information and communication technologies for the exchange of valid information for diagnosis, treatment and prevention of disease and injuries, research and evaluation, and for the continuing education of health care providers, all in the interest of advancing the health of individuals and their communities [25]. WHO also listed four important elements to telemedicine: provide clinical support; intention to overcome geographic barriers; use of several types of information and communication technologies; and improve health outcomes [26]. This model portrays the natural evolution of healthcare in the digital era, resulting in reduction of the distance between two or more locations, promoting access to specific methodologies in addition to reducing the cost of structure. It can also work through live interactive audiovisual links, live video transmission or online viewing of stored education material [27–29].

Brazil is the largest South America country with approximately 3 million live births per year and a significant proportion of infants at high-risk for brain injury [30]. Like any middle-income country, the available resources for neonatal care are unequal. Therefore, telemedicine can be used as a tool for education, consultation, patient care and research. This model allows low-cost access of remote and underserved areas to specific methodologies and expertise [27–29]. Considering that less than 5% of Brazilian NICUs provide well-structured neurocritical care [31], and the implementation of that requires specialized resources, adequate equipment, and qualified personnel, the use of an advanced and protocolized telemedicine model may be a better solution to decrease these disparities. For that, in order to provide neurocritical care to a broader range of Brazilian NICUs, a protocolized telemedicine system called *Protecting Brains and Saving Futures (PBSF) Guidelines* was developed and implemented in some NICUs. The goals of the *PBSF Guidelines* are to establish remote neurocritical care units by providing adequate equipment, specialized training, implementation of standardized protocols, continuous neuromonitoring and expert support, quickly and at low cost.

The aim of this prospective multicenter and observational study is to describe the centers’ adherence to the *PBSF Guidelines* and clinical outcomes over a 3-years period. We hypothesize that the adherence to the *PBSF Guidelines* will increase over time and this will be associated with improvement of clinical outcomes. Results of this study may provide the necessary background information on the use of telemedicine aiming to protect neonatal brains and save futures, and for the development of larger studies and initiatives.

## Materials and methods

### Study design and setting

This prospective, multicenter, and observational study will be performed in the 20 Brazilian NICU’s located at 4 different states, of which 15 are private and 5 are part of the Brazilian free health care system or phylantropic. All units have adopted the *PBSF Guidelines* as a standard-of-care for high-risk newborns and agreed to participate in the study. Data will be collected for a period of 3 years, from Dec 2021 to Nov 2024.

### Ethics approval and consent to participate

The study followed the precepts of good clinical practice and has been performed in accordance with the Declaration of Helsinki. The study proposal was approved by the Research Ethics Committee of the Irmandade da Santa Casa de Misericórdia de São Paulo under the following approval numbers and dates: 3.142.318 on February 12^th^, 2019 (S1 and S2 Files); 3.357.239 on May 30^th^, 2019 (S3 and S4 Files); and 3.506.106 on August 13^th^, 2019 (S5 and S6 Files). In addition, it received formal authorization from the Clinical and Administrative Board of each center. The original protocol approved by ethics is available at S7 File. The written informed consent from parents or guardians will be obtained by trained research investigators prior to inclusion in the study. The same care under the *PBSF Guidelines* will be provided to patients who decline study entry. All data will be treated anonymously and confidentially, and in no phase of the study any name, image, or data that allows participants identification will be disclosed. The study was registered in ClinicalTrials.gov (NCT03786497). It is reported using the Standard Protocol Items Recommendations for Interventional Trials (SPIRIT). The SPIRIT schedule is showed in Fig 1 and the completed SPIRIT checklist is available in S1 Appendix. Any proposed amendments will be discussed with the Research Ethics Committee and each institution’s Clinical and Administrative Board and communicated with all investigators, sponsor, trial participants and trial registry (Clinicaltrials.gov).

**Fig 1 pone.0262581.g001:**
[figure not shown]
Schedule of enrollment, interventions, and assessments.

### Eligibility criteria

In this study, the NICUs eligibility criteria are to have adopted the PBSF guidelines and agree to participate in the study (S2 Appendix). The characteristics of each NICU will be recorded and described. In those NICUs, all infants admitted from birth up to 3 months of age, and submitted to the *PBSF Guidelines* during the study period will be eligible. Indications for the use of the *PBSF Guidelines* are provided on Box 1. The *PBSF Guidelines* is the standard-of-care for high-risk newborns at all these hospitals. Patients with genetic syndromes or malformation incompatible with life will not be included. Details on the *PBSF Guidelines* are provided in (S3 Appendix). Briefly, it includes provision of equipment and resources, connection between the associated NICU and the remote monitoring center called the *Central of Surveillance and Intelligence (CSI)*, training and teaching of all health care professionals of each NICU, and customized multiparametric recordings of biological signals from each patient. At the CSI, a team is available 24 hours a day all year around, allowing for case discussions and simplified reports with brain monitoring information at the patient monitor’s display every 6 hours.

Box 1. Indications for use of the *PBSF Guidelines* in the participating centers.IndicationsExtreme prematurityPeri-intraventricular HemorrhageHypoxic-ischemic encephalopathy (mild, moderate, or severe)Congenital heart diseaseNeonatal strokeCongenital infectionsNosocomial infectionsInborn errors of metabolismSevere hemodynamic/ventilatory instabilitySeizuresBrain malformationsCentral nervous system infectionExtracorporeal membrane oxygenationPBSF, protecting brains and saving futures.

### Variables

Population demographics: gender, type of delivery, gestational age at birth, gestational age ≤ 32 weeks and < 37 weeks, Apgar score at 1 min, 5 min and 10 min, birth weight, current weight, inborn or out born, use of antenatal steroids and magnesium sulfate. Primary diagnosis: seizure, mild HIE, moderate or severe HIE/cooling, neurologic abnormalities or congenital central nervous system (CNS) anomalies, grade III or IV intraventricular hemorrhage (IVH) or hydrocephalus, periventricular leukomalacia, meningitis, neural tube defects, stroke, cyanotic congenital heart defect (CHD), prematurity, gestational age ≤ 32 weeks, meconium aspiration syndrome, cardiorespiratory instability (anemia, shock and respiratory alkalosis/acidosis), necrotizing enterocolitis, metabolic disease, extracorporeal membrane oxygenation (ECMO)/pre-ECMO. For descriptive analysis patients will be divided into two groups accordingly to their primary diagnosis: neurological or clinical. A minimal anonymized data set necessary to replicate future study findings is provided as (S4 Appendix).

### Outcomes

The primary outcomes are detailed on Box 2. Results will be described as n (%) or median [IQR] for the overall population and for each center. Then, we will compare changes over time for the 3 years of data collection within and between centers. Finally, those results will be compared between 2 major groups: neurologic vs clinical patients.

Box 2. Primary outcomes.Adherence to the PBSF GuidelinesUse and duration of aEEG/EEG/NIRS monitoringUse of neuroimaging examsNumber of Sub-specialties consultation (neurology and neurosurgery)Number of primary neurologic or medical patients with aEEG, EEG and/or NIRS monitoring and the duration of the monitoring (hours)Number of primary neurologic or medical patients with brain MRI, neurology consult, and neurosurgery consultNumber of clinical case discussions and videoconference meetingsClinical outcomesNumber of electroencephalographic seizures during hospitalizationUse and types of anticonvulsants administeredUse and types of inotropes and fluid resuscitation administered during NICU stayDeath before hospital dischargeLength of hospital stayNumber of patients referred to high-risk infant follow-up*PBSF, protecting brains and saving futures. *Every attempt will be made to obtain 18–24 months follow-up of these infants, with a Bayley III evaluation.

Secondary outcomes are outlined on Box 3. To address potential source of bias related to financial availability, the outcomes of interest will be also adjusted based on the unit primary profile: private, philanthropic, foundation or public.

Box 3. Secondary outcomes.Descriptive usage of PBSF GuidelinesNumber of remote communications between CSI and local teamNumber of reports issued for aEEG / EEG exams with or without the use of NIRSNumber of patients who performed Therapeutic HypothermiaAdverse effects of brain monitoring expressed by skin lesion due to electrode / sensor positioningPBSF, protecting brains and saving futures; CSI, Central of Surveillance and Intelligence; NIRS, near infrared spectroscopy; aEEG, amplitude integrated electroencephalography; EEG, electroencephalography; MRI, magnetic resonance image; US, ultrasonography.

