### Sample size

Based on our current experience, an average of 5 patients per month with criteria for neurocritical care are admitted on each center, making a total of 3,240 eligible patients during the 3-year period. Considering a 30% loss due to refusal to consent, non-availability of the research team or missing data, we expect to recruit 2,268 infants from all study centers (around 756 patients per year).

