### Statistical methods

Categorical variables will be analyzed by descriptive statistics and presented as number of valid cases and percentage (%). Numeric variables will be analyzed as mean and standard deviation, median and interquartile ranges, or confident intervals. Since, it is possible that the patient population is quite different across the sites, analyses for the overall population will account for site differences or for the possibility of correlated observations within a site.

To compare adherence and outcomes over time (i.e., between years 1, 2 and 3) the following statistical approach will be applied: a) a test for normality in each category using the Shapiro-Wilks (<50 observations) or Kolmogorov–Smirnov, b) if normality assumption holds, a Welch’s F test will be done, c) if normality assumption still holds the ANOVA with post hoc Bonferroni will be performed. If the normality assumption is violated, a non-parametric test (Kruskal–Wallis) will be used to analyze categorical variables and for significant differences between the two groups (neurological vs clinical). A final *p* value of <0.05 will be considered statistically significant. Analysis of variability (distribution) per site for each variable of the 2 main outcomes will also be performed and Run Chart will be generated to follow the evolution of the outcomes over time for the 2 groups of patients: neurologic and clinical. All analysis will be done using the StataCorp. 2021. Stata Statistical Software: Release 17. College Station, TX: StataCorp LLC.

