Brazil allows several opportunities for telemedicine implementation, expanding the actions of healthcare professionals and integrating healthcare services [86]. We developed the *PBSF Guidelines* with a surveillance and intelligence center to support clinical decisions across the country. Telemedicine has been used by our group in the past few years to promote educational training and remote neuromonitoring but its impact on clinical outcomes needs to be formally evaluated. Thus, results of this 3 years prospective, multicenter, and observational study will help to determine the incidence of neonatal problems associated with brain injury and disabilities, the incidence of clinical and subclinical seizures, detection of brain hemodynamic/oxygenation instability and associated interventions. The study will be limited to the 20 NICUs using the *PBSF Guidelines* and variability in clinical practices, experience of health care providers and staffing of the units, will be analyzed as it may affect some of the outcomes. Enrollment of such large number of patients will require a strong coordination between the central unit and all 20 centers, which has already been established by the CSI. Practical or operational issues will be to assure that all eligible patients are identified in a daily basis and approached for consent. Data collection requires careful training of data extractors and timely and precise data entry. A computerized and safe double-checking system has been developed. Biological signals will be continuously collected and stored at the CSI and multimodal signal analysis has been developed. Although low, there are costs for the implementation and use of the *PBSF Guidelines*. Thus, an adjusted analysis based on the profile of the units will be performed as costs might represent a limitation on the generalizability of the study findings. A future cost/benefit analysis is under planning.

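### Center-by-year rates of uncommon outcomes rest on about 38 infants each, and the stated methods do not separate chance from real differences between centers

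*Protocol article*

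**What the plan says.** The abstract gives the primary objective as describing adherence and clinical outcomes by center and over three years. The Outcomes section first reports each result as a count with percentage, or a median with interquartile range, overall and per center. It then states: "Then, we will compare changes over time for the 3 years of data collection within and between centers".

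Statistical methods adds: "Analysis of variability (distribution) per site for each variable of the 2 main outcomes will also be performed". For the comparison of years 1, 2 and 3 it names normality tests followed by Welch's F, ANOVA with Bonferroni, or Kruskal–Wallis, at p < 0.05. Site differences or within-site correlation are to be accounted for, but that sentence covers only analyses of the overall population. Mixed-effects models are named once, under Missing data.

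On numbers, Sample size says "we expect to recruit 2,268 infants from all study centers (around 756 patients per year").

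**The concern.** A comparison within and between centers, by year, divides the cohort into 20 x 3 = 60 cells. With a few dozen infants per cell, the observed rate of an uncommon event moves a great deal even when nothing differs or changes. The tests named for the time comparison do not estimate how much of the spread between centers is real, and the article's provision for site stops at the overall analysis.

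At stake is the center-level part of the primary objective: how far centers differ in outcomes such as death, and which centers changed over three years. Without an estimate of true between-center variation, the observed spread cannot answer either question.

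**Working it through.** **1. Infants per center-year.** Inputs from Sample size: "an average of 5 patients per month with criteria for neurocritical care are admitted on each center", and "making a total of 3,240 eligible patients during the 3-year period". The abstract, Study design and setting, and the Discussion all give 20 centers.

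- Stated route: 3,240 x 0.70 = 2,268; 2,268/3 = 756 per year; 756/20 = **37.8** per center-year.
- The eligible total does not reproduce with 20 centers: 5 x 36 x 20 = 3,600, whereas 5 x 36 x 18 = 3,240. The number of centers and the total need to be reconciled.
- Alternatives: 756/18 = 42, and 5 x 12 x 0.70 = 42. The result below is much the same at 38 and 42.

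**2. Precision of one center-year rate.** SE = sqrt(p(1 − p)/n). The article gives no outcome rates, so a range is assumed. The last column simulates 20 centers with the same unchanging true rate (20,000 replicates). It gives the mean number of centers whose rate at least doubles or at least halves between two years.

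| Assumed true rate | SE, n = 38 | SE, n = 42 | Centers of 20 halving or doubling by chance, n = 38 |
|---|---|---|---|
| 5% | 3.5 points | 3.4 | about 13 |
| 10% | 4.9 | 4.6 | about 9 |
| 20% | 6.5 | 6.2 | about 4 |
| 50% | 8.1 | 7.7 | about 0 (0.1) |

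At 10%, the line is sqrt(0.10 x 0.90/38) = 0.049. The lowest and highest of the 20 observed rates then average about 2% and 20% in a single year, although every center is identical. With n = 42 about 8 centers halve or double instead of about 9.

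**3. Power within one center.** Year against year with 38 infants each, two-sided 0.05: a fall from 20% to 10% is detected with 23% power, and from 10% to 5% with 13%. The first would need 199 infants per year for 80% power. A large change is detectable: 60% to 90% has 87% power.

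**4. How much of the observed spread is real.** Real share of variance = τ²/(τ² + p(1 − p)/n), where τ is the true between-center SD, which the article does not give. At p = 10% and n = 38, the sampling variance is 0.09/38 = 0.00237.

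- τ = 3 points: 0.0009/(0.0009 + 0.00237) = 28%
- τ = 5 points: 0.0025/(0.0025 + 0.00237) = 51%
- τ = 10 points: 0.0100/(0.0100 + 0.00237) = 81%

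The break-even τ equals the SE: about 5 points at a 10% rate and about 8 at a 50% rate.

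**5. Whole network.** With 756 infants per year, 10% against 5% has 96% power, ignoring clustering. The difficulty is confined to center-level results.

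**The case against.** A reader might infer that raw center rates will mostly show chance and will be taken for real variation or change. The documents do not support that. The first half depends on τ and the outcome rate, neither of which is given. The article itself points to heterogeneity: 15 private and 5 public or philanthropic units, populations that may differ markedly across sites, and variation in practice, experience and staffing. At τ = 10 points the spread is mainly real. The second half is a guess about interpretation, since no ranking, labelling of centers or p-value per center is announced.

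Many primary outcomes are also not proportions. Monitoring hours, numbers of consultations and meetings, and length of stay fall outside the binomial figures. The plain per-center description is not split by year. Over three years each center has about 113 infants (2,268/20), and at a 10% rate with τ = 3 points the real share rises to 53%. The overall analysis does account for site, outcomes are to be adjusted for unit profile, and an analysis plan not shown may add center-level modelling.

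These points stand and narrow the concern to uncommon binary outcomes by center and year. They do not remove it. The comparison within and between centers over the three years is stated, and the methods the article names for comparing years do not separate sampling variation from true center differences. Adjusting for unit profile does not do so either. Without an estimate of τ, nobody can tell which of the cases above applies.

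**Conclusion.** The point holds for center-level, year-by-year comparison of uncommon binary outcomes. With about 38 infants per center-year on average (42 on the alternative counts), a center's rate carries a standard error of 3.5 to 6.5 points at assumed true rates of 5% to 20%. Between about 13 and 4 of 20 unchanged centers would then appear to halve or double between two years. The average also hides low-volume centers and the planned neurologic/clinical split: with 19 infants the SE at a 20% rate is 9.2 points.

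The figures rest on assumed outcome rates, equal center sizes and binomial variation. No claim is made about which source of variation dominates, and the network-level time trend is not in question. This is an inexpensive improvement to center-level results rather than a flaw in the study's main inference.

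**What to change.** For the comparisons within and between centers, specify a mixed model with a random center intercept and a random center time slope, using a link suited to each outcome (for example logistic for death, a count model for numbers of consultations). Report:

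- the between-center SD and the SD of slopes, each with a 95% CI;
- partially pooled center estimates;
- the raw center results beside them, with exact CIs or funnel limits for proportions, labelled descriptive.

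No new data are needed. The article already names mixed models and Stata 17, so the cost is a paragraph in the analysis plan and some modelling time. The downside is that estimates for small outlying centers are pulled toward the mean, which is why the raw results stay alongside. The gain can be sized: at a 10% rate and τ = 3 points, the root mean squared error of a center-year estimate falls from 4.9 points to sqrt(0.00237 x 0.275) = 2.6 points. It is smaller when τ is larger.

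### The only test named for neurologic versus clinical patients compares outcome levels and cannot show whether their changes over the three years differ

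*Protocol article*

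**What the plan says.** The Outcomes section sets out three steps. Results are first described overall and by center. The second step is: "Then, we will compare changes over time for the 3 years of data collection within and between centers". The third is: "Finally, those results will be compared between 2 major groups: neurologic vs clinical patients".

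In Statistical methods, the relevant paragraph opens: "To compare adherence and outcomes over time (i.e., between years 1, 2 and 3) the following statistical approach will be applied". It lists normality tests, Welch's F and ANOVA with Bonferroni comparisons. If normality fails, "a non-parametric test (Kruskal–Wallis) will be used to analyze categorical variables and for significant differences between the two groups (neurological vs clinical". No year-by-group term, or other test of a difference in change, is named.

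Four further statements bear on the point:

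- Statistical methods plans a display by group: "Run Chart will be generated to follow the evolution of the outcomes over time for the 2 groups of patients: neurologic and clinical".
- Variables gives the purpose of the split: "For descriptive analysis patients will be divided into two groups accordingly to their primary diagnosis: neurological or clinical".
- Statistical methods says that analyses of the overall population will allow for site differences or for correlation within a site.
- Missing data mentions mixed effect models, as a way of handling missing values, without listing their terms.

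**The concern.** The sentence on the two groups follows directly on the sentence about changes over three years, and the two-group test sits in the paragraph on comparing years 1, 2 and 3. A reader will expect the group comparison to cover change. The named test has no year in it. It asks whether outcome values are distributed differently in neurologic and clinical infants.

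For several primary outcomes in Box 2, such as brain MRI and neurology consultation, a difference in level is to be expected from the diagnoses that define the groups. A small p-value there reflects case mix. Reported alongside a comparison of years, it could be taken as evidence that the groups evolved differently. A large p-value could likewise hide the fact that only one group changed.

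**Working it through.** **What the test can measure.** Patient outcomes are recorded over a hospital stay, so an infant normally belongs to one study year and has no year-1-to-year-3 change of its own. A two-group Kruskal-Wallis test on infants' outcomes therefore compares levels, whether the years are combined or taken one at a time. A difference in change is a contrast of four group-by-year cells:

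(neurologic year 3 − neurologic year 1) − (clinical year 3 − clinical year 1)

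**Inputs.** Sample size gives 2,268 infants, about 756 per year: 3,240 × 0.70 = 2,268 and 2,268 / 3 = 756. The 3,240 does not follow from 20 centers (20 × 5 × 36 = 3,600, giving 2,520 after loss and 840 per year); it fits 18 centers (18 × 5 × 36 = 3,240). That is a separate matter. I use 756 and show below that 840 changes nothing here.

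Assumptions not in the article: equal groups (378 per group per year, 1,134 per group in all), the percentages below, and no clustering by site. For a yes/no outcome, the two-group Kruskal-Wallis statistic equals z² × (N − 1)/N, so the two-proportion z is practically the same test.

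**Illustration A: same change, different level.** Neurologic 60/70/80%, clinical 40/50/60%.

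- All years together: 0.70 vs 0.50, SE = sqrt(2 × 0.60 × 0.40 / 1134) = 0.0206, z = 0.20 / 0.0206 = 9.72.
- Year by year, with the pooled-proportion SE and 378 per group: z = 0.20 / 0.0364 = 5.50, 0.20 / 0.0356 = 5.61 and 0.20 / 0.0333 = 6.00.
- Difference in change: 0.20 − 0.20 = 0.

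**Illustration B: different change, same three-year average.** Neurologic 50/60/70%, clinical 60/60/60%.

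- All years together: 0.60 vs 0.60, z = 0.
- Year by year: z = −0.10 / 0.0362 = −2.76, then 0, then 0.10 / 0.0347 = 2.88.
- Difference in change: 0.20, SE = sqrt((0.25 + 0.21 + 0.24 + 0.24) / 378) = 0.0499, z = 4.01, p = 0.00006, 95% CI 0.20 ± 1.96 × 0.0499 = 10 to 30 points.

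In B the yearly tests do show a gap that reverses sign, but none of them estimates or tests the change. In A they are all strongly significant although the changes are identical.

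With 840 infants per year each z rises by sqrt(840/756) = 1.054, to 10.2 (A, all years) and 4.2 (B, difference in change).

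**Simulation.** 2,000 runs per scenario, 756 infants per year, normal outcome with SD 1, alpha 0.05, no site clustering, neurologic share 30%, 50% or 70%. The interaction is the 2-df year-by-group F test. Entries are rejection rates.

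| Scenario | Kruskal-Wallis, all years | Kruskal-Wallis, each year | Year-by-group term |
|---|---|---|---|
| Parallel trends, constant gap 0.3 SD | 100% | 96–98% | 4.1–5.6% |
| One group flat, other from −0.2 to +0.2 SD | 4.6–4.9% | 70–76% in years 1 and 3, about 5% in year 2 | 90–94% |

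**The case against.** The strongest reply is that the plan does not unambiguously promise a comparison of changes between the groups. The explicit promise on change is within and between centers. The results compared between groups could be the n (%) and median [IQR] summaries of the first step, and Box 2 itself lists counts for neurologic and medical patients as outcomes. For those, a test of levels fits. Variables calls the split descriptive, the run charts show each group over time, and an article may leave model terms to a fuller document. The figures above rest on invented percentages and show the general fact that a main effect is not an interaction.

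Much of this stands, and it limits the point. Four stronger readings are tempting but are not supported:

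- A reader might infer that the test pools all three years. The article does not say so, and the blindness of the test in illustration B depends on it.
- A reader might infer that the group test is meant to bear on the study hypothesis. The Introduction says that adherence "will increase over time and this will be associated with improvement of clinical outcomes". It says nothing about a difference between neurologic and clinical infants.
- A reader might extend the point to every outcome. Case discussions and videoconference meetings are plausibly center-level counts with no clear split by group.
- A reader might conclude that levels must be shown without p-values. That is a preference.

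The reply does not remove the mismatch. The order of the sentences in Outcomes makes change part of what is compared, and the group test is placed under the comparison of years. Run charts give no estimate or interval for a difference in change. A descriptive purpose also sits uneasily with testing the same split for significant differences. Nor is the point only that detail is missing: the article names a specific test, and that test does not fit.

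**Conclusion.** The point holds in a limited form. On the natural reading of Outcomes, changes over three years are among the results compared between neurologic and clinical patients, and the one test named for the two groups addresses levels only. This does not depend on whether years are combined: with parallel trends and a 0.3 SD gap, the test rejects in 100% of simulated runs on all years and in 96–98% within a single year, where a test of the year-by-group term rejects in about 5%. When one group changes and the other does not, with equal averages, the test on all years rejects in about 5% and the year-by-group test in 90–94%. These rates rest on assumed effects, group shares of 30–70%, and no site clustering, which would alter the numbers but not what each test measures. If the authors intend only levels to be compared, the test answers their question, but its result is largely case mix and should be described so. The weakness is worth correcting; it does not undermine the comparison of years itself.

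**What to change.** In Statistical methods:

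- State that the neurologic-versus-clinical comparison of changes, for patient-level outcomes, uses a year-by-group term in the model that accounts for site.
- Report the change over the years in each group, and the difference in change with a 95% CI.
- Label any two-group Kruskal-Wallis result as a comparison of levels that reflects case mix, not as evidence on change.
- Say in Outcomes which results are compared between the groups: levels, changes or both.

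The cost is one extra model term per outcome, and precision: in illustration B the standard error of the difference in change is 0.0499, against 0.0206 for the difference in level over all years, about 2.4 times as large. Fewer group comparisons will reach significance.
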